#### Statistical and Qualitative Analysis

Our expectation for the primary outcome is the reduction and stabilization of blood pressure. For the secondary outcome, we hope for acceptance of the eHealth platform and improvements in treatment adherence, physical activities, and dietary intake. A priori levels will be set according to the assessment tool and the expected outcome. The acceptance of the eHealth platform will consider good scores obtained in the analysis of usage logs and questionnaires of engagement, SUS, and TAM. Improved adherence to treatment will consider MBG questionnaire scores measured before and after the intervention. For the analysis of physical activities and dietary intake, a binary outcome will consider whether the patient has adequate levels, diagnosed according to the SISVAN’s questionnaire and standards.

For qualitative data, we will use Minayo’s guidelines [30]. Numeric data will be analyzed with statistical software SPSS 22 (IBM Corp, Armonk, New York). We will calculate the measures of central tendency and dispersion of the quantitative variables, and we will use the Kolmogorov-Smirnov test to verify normality. Basic quantitative data will be determined by mean, standard deviation, and median. Categorical data will be determined by simple frequency. Blood pressure data will be analyzed with the paired *t* test. Either the paired *t* test (parametric) or the Wilcoxon test (nonparametric) may be applied to compare other quantitative variables before and after the intervention. To assess treatment adherence, physical activity, and dietary intake after intervention, we will apply the Chi-square test while considering the app use as the dependent variable; the independent variables will be treatment adherence, physical activity, and dietary intake. For the MBG questionnaire, we will apply the Mann-Whitney test to compare the score between the groups before and after the intervention. The same test may be used to compare diastolic and systolic blood pressure measurements between the preintervention and postintervention groups. We will consider a 95% confidence interval (*P*<.05).

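### Treatment adherence gets two planned tests at P<.05, a Chi-square on an after-only category and a Mann-Whitney on the MBG score, and neither is named as deciding

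*Protocol article*

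**What the plan says.** All the relevant sentences stand in the Statistical and Qualitative Analysis section of the protocol article.

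- Definition of adherence: "Improved adherence to treatment will consider MBG questionnaire scores measured before and after the intervention".
- First test: "To assess treatment adherence, physical activity, and dietary intake after intervention, we will apply the Chi-square test". App use is the dependent variable, and "the independent variables will be treatment adherence, physical activity, and dietary intake".
- Second test: "For the MBG questionnaire, we will apply the Mann-Whitney test to compare the score between the groups before and after the intervention".
- Binary rule: "For the analysis of physical activities and dietary intake, a binary outcome will consider whether the patient has adequate levels". No such rule is given for adherence.
- Levels in general: "A priori levels will be set according to the assessment tool and the expected outcome".
- Significance: "We will consider a 95% confidence interval (*P*<.05", stated once for all analyses.

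The MBG questionnaire is the only adherence instrument in the protocol. It is collected from both groups before the intervention (Preintervention Period) and again afterwards (Postintervention Period).

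**The concern.** The Chi-square test needs adherence as a category, measured after the intervention. The definition and the Mann-Whitney sentence treat it as a score. Both tests are firm commitments on the same questionnaire, and the section does not say which result answers whether adherence differed between groups.

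The adherence result could therefore be positive on one test and negative on the other, with no rule for reading the pair. The trial is nonblind, and the plan allows analysis techniques to be modified in the light of the collected data, so the choice could be made after the results are seen. Two chances at P<.05 also raise the false-positive rate for this outcome.

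Baseline matters as well. Under Study Population and Sample, groups are formed largely by whether the patient owns a compatible phone. The variables listed for the propensity score are age, gender and socioeconomic status, not baseline adherence. An after-only comparison therefore takes no account of adherence differences present at the start, although the plan collects the score that would show them.

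**Working it through.** **Inputs from the protocol.** 28 per group before the loss allowance and 34 after it; significance at P<.05, taken as two-sided.

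**The plan's own figure.** The 28 belongs to the primary outcome (80% against 40%); no power is stated for adherence. Without continuity correction:

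n = [1.96·√(2·0.6·0.4) + 0.8416·√(0.8·0.2 + 0.4·0.6)]² / 0.4² = (1.358 + 0.532)² / 0.16 = 22.3, so 23.

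With continuity correction: (22.3/4)·[1 + √(1 + 4/(22.3·0.4))]² = 27.1, so 28. Then 28 × 1.2 = 33.6, so 34. Both figures reproduce.

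**Assumptions, because the documents give no values.** Normal MBG scores with equal SD, groups alike at baseline, a two-category cut at the 30th, 50th or 70th percentile of the control group, and both tests applied to the post-intervention score. The shift of 0.78 SD is one that the Mann-Whitney test detects with close to 80% power.

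**Power of the Chi-square test.** The share above the cut is p0 in the control group and p1 = Φ(0.78 − z) in the intervention group, where z is the cut in SD units. Then

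power = Φ{ [(p1 − p0) − 1.96·√(2p̄(1 − p̄)/28)] / √([p0(1 − p0) + p1(1 − p1)]/28) }.

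| Cut (control percentile) | p0 | p1 | Chi-square, formula | Chi-square, simulated | Mann-Whitney, simulated | Tests disagree, simulated |
|---|---|---|---|---|---|---|
| 30th | 0.70 | 0.904 | 48% | 48% | 79% | 37% |
| 50th | 0.50 | 0.782 | 60% | 61% | 79% | 22% |
| 70th | 0.30 | 0.601 | 62% | 62% | 79% | 21% |

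The simulation used 10,000 runs per cell. Repeat runs agree within about two percentage points; at the 30th percentile, disagreement came out at 35% to 37%. As a check on the Mann-Whitney figure, the large-sample value is Φ(0.78·√14·√(3/π) − 1.96) = Φ(0.89) = 81%, close to the simulated 79%.

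**Direction of the disagreement.** The share of trials in which only the Chi-square test is significant equals (disagreement − power difference)/2: (37 − 31)/2 = 3%, (22 − 18)/2 = 2% and (21 − 17)/2 = 2%. When an effect exists, nearly all the disagreement is the category missing what the score finds.

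**No true effect.** Singly, the Mann-Whitney test rejects in 4.7% to 4.9% of trials and the Chi-square test in 4.5% to 5.3%. At least one rejects in 7.0% to 7.8%. This lies where it should, between 5% for identical tests and 1 − 0.95² = 9.75% for independent ones.

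**If the score test is read as a test of change.** The wording of the Mann-Whitney sentence would also allow this. With a shift of 0.75 SD, 28 per group and a central cut, the Chi-square test has about 59% power. A Mann-Whitney test on change has 61%, 77% and 93% at before-after correlations of 0.3, 0.5 and 0.7. The gap is then about 2, 18 and 35 points.

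**The case against.** The strongest reply is that there is no contradiction. The definition names an instrument and two time points; it does not say that adherence may never be grouped, and a category derived from the MBG score still uses that score. The general sentence, "A priori levels will be set according to the assessment tool and the expected outcome", could supply a cut, and a score and a category can be complementary summaries. The article is condensed, so the cut-off may sit in an analysis plan that is not shown. Two tests announced in public are also harder to suppress than one chosen silently.

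Much of this stands. The missing cut-off is no finding, and the two definitions need not be called incompatible. What remains is that the printed text commits to two tests of one outcome without ranking them. A cut-off supplied later would make the Chi-square test possible but would not say which test decides. Announcing both does not settle how a split result is to be read.

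A reader might go further and infer that the outcome will receive conflicting verdicts, or that the trial loses much of its power for adherence. The documents support neither. Disagreement is possible, not certain. The Mann-Whitney test on the score is already planned, so the Chi-square test is an addition and the score's information is kept. How far the Chi-square test falls short depends on a cut, an effect and, for a change score, a correlation that the protocol does not give; at a correlation of 0.3 the gap to a change score nearly vanishes.

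The sentence that reads "Either the paired *t* test (parametric) or the Wilcoxon test (nonparametric) may be applied to compare other quantitative variables before and after the intervention" is permissive and concerns comparisons over time, so it is not counted here as a further committed test of adherence between groups.

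**Conclusion.** The point holds as a matter of two unranked tests on one secondary outcome, with the Chi-square test on adherence lacking support in the section's own definitions. Under the stated assumptions the Chi-square test is the weaker of the two, the verdicts split in roughly a fifth to over a third of trials when the effect is 0.78 SD, and the false-positive rate for adherence rises by two to three percentage points when there is none. These sizes are illustrative, since no MBG effect, SD or cut-off is given. They also assume groups alike at baseline, which allocation by phone ownership does not secure. The primary outcome and the sample size are untouched. The change is worth making because it is small and settles in advance which adherence result counts.

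**What to change.** In Statistical and Qualitative Analysis:

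1. Limit the Chi-square sentence to physical activity and dietary intake, the two outcomes that have a binary rule.
2. Name one deciding analysis for adherence: the post-intervention MBG score compared between the allocated groups, adjusted for the baseline MBG score. This keeps the before-and-after definition and says how baseline is used. It adjusts for measured baseline adherence only, not for other differences that come with phone ownership.
3. Show the share of patients in each MBG category descriptively, or label any test on the categories as supportive.

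The cost is a few sentences. No new data, visits or patients are needed, because the MBG score is already collected at both times. The downside is that the categorical display of adherence carries no confirmatory P value.

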### Nonrandomized Controlled Trial

This is an applied research of technological innovation with software development and analysis of its effects through a controlled, nonrandomized, nonblind, prospective, and monocentric clinical trial. The Research Ethics Committee of the University of Passo Fundo, Rio Grande do Sul, Brazil (report 3.414.793) approved this project, which was registered in the Brazilian Platform of Clinical Trials under the code RBR-2rkkgn (Universal Trial Number U1111-1230-7550). Figure 2 presents the trial design and flowchart.

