#### Study Population and Sample

The study population will include men and women under treatment for arterial hypertension who will be assisted by health professionals in the public health system of a Brazilian city. After the invitation to take part in the study, the participants will sign a consent form. The effect (primary outcome) is expected to be 80% in the intervention group and 40% in the control group, which means a 40% difference. These proportions are based on the findings of the study by Neumann et al [22], which was conducted with a similar design, and also on more optimistic results obtained from one of our pilots [19]. For sample calculation, we used Epi Info version 6.0 software (Centers for Disease Control and Prevention, Atlanta, Georgia; sample size/2 proportions). We considered an estimate of 40% proportion difference between groups, 95% confidence interval, and 80% statistical power (beta). The calculation resulted in 28 individuals for each group, but to minimize the effects of loss and refusal during the intervention, we added 20% to the size, yielding a total of 34 individuals in each group.

The allocation of patients in each group will be based on the eligibility criteria. For example, if the patient fits all the criteria but does not have a mobile phone compatible with the app, then he or she will be allocated to the control group. If the patient has a mobile phone compatible with the app, he or she will be allocated to the intervention group. For propensity score calculation, based on the effect of confounding factors or predictors of exposure (to intervention), we will consider demographic variables of age, gender, and socioeconomic status.

We will consider the following inclusion criteria:

Cognitive ability confirmed by the Mini-Mental State Examination [23] (both groups)Current medical monitoring for the treatment of hypertension in the public health system of the city of Passo Fundo, RS, Brazil (both groups)Possibility to measure blood pressure in drugstores, hospitals, Family Health Strategies, or centers for comprehensive health care (both groups)Possession of an Android mobile phone, version 4.3 or higher (intervention group)Familiarity with the use of apps (intervention group)Internet access on the smartphone (intervention group).

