#### Preintervention Period

After verifying the inclusion criteria, all participants will have a 1-hour meeting with the researchers for instructions on the objective of the study and for signing a consent form detailing all the study procedures. We will register the participants of the intervention group in the system and instruct them about the app’s use. We will collect the preintervention data from both groups from a sample characterization questionnaire and an MBG questionnaire [24].

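### The between-group MBG adherence tests do not adjust for the baseline score, so in this nonrandomized design any starting difference carries into the apparent app effect; adjustment reduces that bias but may not remove it

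*Protocol article*

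**What the plan says.** All references are to the Methods of the Protocol article.

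- **Design** (Nonrandomized Controlled Trial): "analysis of its effects through a controlled, nonrandomized, nonblind, prospective, and monocentric clinical trial".
- **Allocation** (Study Population and Sample): "If the patient has a mobile phone compatible with the app, he or she will be allocated to the intervention group". The intervention group must also be familiar with apps and have internet on the smartphone.
- **Data** (Preintervention Period): "We will collect the preintervention data from both groups from a sample characterization questionnaire and an MBG questionnaire". MBG is collected again in the Postintervention Period.
- **Between-group tests** (Statistical and Qualitative Analysis): "For the MBG questionnaire, we will apply the Mann-Whitney test to compare the score between the groups before and after the intervention". In addition: "To assess treatment adherence, physical activity, and dietary intake after intervention, we will apply the Chi-square test".
- **Definition of improvement** (same section): "Improved adherence to treatment will consider MBG questionnaire scores measured before and after the intervention".
- **Confounding** (Study Population and Sample): for a propensity score, "we will consider demographic variables of age, gender, and socioeconomic status". Baseline MBG is not among these variables, and no outcome analysis is said to use the score.

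**The concern.** Read as written, the groups are compared once at baseline and once afterwards, and neither comparison uses the other measurement. A result that is not significant before and significant after is not an estimate of an effect. The chi-square uses post-intervention values only, and it needs the score cut into categories.

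In a randomized trial, leaving out the baseline score would mainly cost precision. Here the groups exist before the intervention and differ by construction in phone, app experience and internet access. If they also differ in adherence at the start, the post-intervention comparison mixes that difference with whatever the app does. Adherence is one of the outcomes the abstract says will be compared, so the reported result for it could mislead.

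**Working it through.** **1. The plan's own figure.** The article gives no calculation for MBG. Its sample size is for the primary outcome (80% v 40%, 80% power, 5% level) and it reproduces:

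- Uncorrected, two-sided: n = [1.96·√(2·0.6·0.4) + 0.8416·√(0.8·0.2 + 0.4·0.6)]² / 0.4² = (1.358 + 0.532)² / 0.16 = 22.3.
- With continuity correction: (22.3/4)·[1 + √(1 + 4/(22.3·0.4))]² = 27.1, so 28 per group.
- 28 × 1.2 = 33.6, so 34 per group.

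I use 28 per group for the check below.

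**2. Assumptions not in the article.** Baseline gap d = 0.3, 0.5 or 0.8 SD. Pre-post correlation ρ = 0.5 or 0.7. Normal scores with SD 1. No app effect.

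**3. What each analysis estimates when the app does nothing.** Two courses of the gap are considered. Either it regresses (post-intervention gap ρd), or it is stable (post-intervention gap d).

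| Analysis | Gap regresses | Gap stable |
|---|---|---|
| Post score only | ρd | d |
| ANCOVA on baseline score | 0 | (1−ρ)d |
| Change score | −(1−ρ)d | 0 |

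With d = 0.5 and ρ = 0.7, post-only is off by 0.35 or 0.50 SD, ANCOVA by 0 or 0.15 SD, and change score by −0.15 or 0 SD.

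**4. Simulated rejection rates with no app effect** (4000 trials per cell, 28 per group, 5% level; Monte Carlo standard error at most 0.8 percentage points). Entries are for d = 0.3 / 0.5 / 0.8.

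| Course of gap | ρ | Mann-Whitney, post only | ANCOVA |
|---|---|---|---|
| Regresses | 0.5 | 8.5 / 14.1 / 29.9% | 5.5 / 5.1 / 5.0% |
| Regresses | 0.7 | 11.6 / 23.4 / 51.2% | 5.1 / 4.3 / 5.3% |
| Stable | 0.5 | 18 / 42 / 81% | 10 / 18 / 33% |
| Stable | 0.7 | 20 / 43 / 81% | 8 / 11 / 21% |

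Repeat runs move the extremes by about a point or two; the ranges quoted elsewhere in this point (8-52%, 18-81%, 8-35%) allow for that. A t test on change scores stays at about 5% when the gap is stable, but rejects in 7-31% when it regresses. With no gap, the post-only Mann-Whitney holds its level (4.8-4.9%).

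**5. More patients do not help.** At 34 per group, ρ = 0.7 and a regressing gap of 0.5 SD, the post-only rate is 28.0%, against 23.4% at 28 per group.

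**6. The baseline test is a weak safeguard.** At 28 per group it detects a 0.5 SD gap in 42-43% of trials and so misses it in 57-58%. It detects a 0.3 SD gap in 18-20%.

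**7. Precision.** With no gap and a true effect of 0.5 SD, power is 41% (Mann-Whitney) v 54% (ANCOVA) at ρ = 0.5, and 43% v 72% at ρ = 0.7.

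**The case against.** **The imbalance is assumed.** A reader might infer that the intervention group will start with different adherence, or that patients select themselves into groups. The article supports neither. Allocation follows eligibility criteria, and nothing links phone ownership to MBG score. This stands: a gap is possible, its size and direction are unknown, and the rates above are conditional on it.

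**Adjustment is no cure.** A reader might infer that ANCOVA restores the 5% level. It does so only if the gap regresses as the model assumes. For pre-existing groups a stable gap is at least as plausible, and ANCOVA then rejects in 8-35% of trials with no effect. A rank-based or bootstrap version deals with skewness, not with this bias. This stands and limits the claim. ANCOVA still rejected less often than the post-only test in every simulated case with a gap.

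**The plan does not ignore the baseline throughout.** Improvement is defined from both measurements, and the optional paired t or Wilcoxon tests could include MBG. The Mann-Whitney sentence might even be meant as a comparison of change. But the paired tests work within groups, and the sentence speaks of the score, not its change. The ambiguity itself needs resolving.

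**Confounding is handled elsewhere.** The propensity score omits baseline MBG and is tied to no outcome analysis. The logistic regression, planned only if feasible, has app use as dependent variable and so yields no baseline-adjusted effect on MBG. The general permission to modify techniques commits to nothing.

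**A condensed article may leave the model to a fuller plan.** That would excuse silence. Here the article names the test, the variable and the time points.

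**Testing the baseline has some purpose in a nonrandomized study.** Checking comparability is reasonable, but a non-significant result is poor reassurance at this size.

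**Conclusion.** The point holds in a limited form. The stated between-group tests of MBG use no baseline adjustment, although the baseline score is available in both groups and the groups are not randomized. If the groups start apart, the post-only test carries over part of the gap (if it regresses) or all of it (if it is stable). Under the assumed gaps and correlations with 28 per group, this means about 8-52% or 18-81% false positives, against about 5% or 8-35% with ANCOVA. These figures show direction and possible size; they are not this trial's error rate. With no gap, the 5% level is kept and only precision is lost.

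The documents do not show that an imbalance is likely, and adjustment is not guaranteed to remove the bias. MBG is a secondary outcome, so the sample size and the primary comparison are untouched. The change should be made, but it does not decide the validity of the trial.

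**What to change.** 1. Make the main between-group MBG analysis one model: post score on allocated group, baseline MBG, age, gender and socioeconomic status (the propensity variables already named). Report the adjusted difference with its 95% CI. Use a rank-based or bootstrap version if the score is skewed.
2. State the ANCOVA assumption: apart from any app effect, patients with the same baseline score and covariates would have the same expected post score in either group.
3. Add a between-group comparison of change scores as a sensitivity analysis. It is unbiased when the gap is stable, the case in which ANCOVA is not. Agreement between the two strengthens the result; disagreement should be reported as uncertainty.
4. Drop the chi-square on adherence as a separate test of effect.
5. Describe baseline MBG by group, and do not take a non-significant baseline test as evidence of comparability.

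**Cost:** analysis wording only, with no new data or patients. Residual confounding and dependence on the ANCOVA assumption remain and must be acknowledged in the report.

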**Methods:**

The platform will include a server that centralizes all the data and business rules, a website dashboard for health professionals, and a mobile app for patients. We will analyze the effects of its use through a controlled, nonrandomized, nonblind, prospective, monocentric clinical trial. We will enroll 68 participants diagnosed with arterial hypertension and under medical follow-up and categorize them into two groups. The participants of the intervention group will use the platform as a monitoring method, whereas the participants of the control group will use conventional methods. In both groups, we will assess and compare the evolution of blood pressure and treatment adherence before, during, and after the intervention.

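### The optional Mann-Whitney test for blood pressure is worded as a comparison of two readings on the same patients; read as intervention versus control at each time it is valid, but it does not test the difference in change.

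*Protocol article*

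**What the plan says.** All the tests are in the Statistical and Qualitative Analysis section of the protocol article.

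- **Blood pressure, firm statement:** "Blood pressure data will be analyzed with the paired" t test.
- **Other before-after comparisons:** the paired t "test (parametric) or the Wilcoxon test (nonparametric) may be applied to compare other quantitative variables before and after the intervention". Wilcoxon is thus named for variables other than blood pressure.
- **Adherence score:** "For the MBG questionnaire, we will apply the Mann-Whitney test to compare the score between the groups before and after the intervention".
- **Blood pressure again, as an option:** "The same test may be used to compare diastolic and systolic blood pressure measurements between the preintervention and postintervention groups". The test referred to is Mann-Whitney, from the preceding sentence.

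The abstract's Methods paragraph describes an intervention and a control group, each followed over time: "In both groups, we will assess and compare the evolution of blood pressure and treatment adherence before, during, and after the intervention". Study Population and Sample allocates by possession of a compatible phone and bases the propensity score on age, gender and socioeconomic status.

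**The concern.** Blood pressure is the primary outcome. The optional sentence names two groups that do not exist in this design: preintervention and postintervention are two occasions on the same patients. An independent-samples test applied to them ignores the pairing. It also sits beside a firm commitment to a paired test, with no rule for choosing between the two. A normality check is planned, so a nonparametric alternative may well be needed, and the only one the section names for blood pressure is the unpaired test.

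The sentence may instead mean intervention versus control, once before and once after, as for the MBG score. Then the test fits the samples but not the question. The abstract promises to compare how blood pressure and adherence evolve. One test at baseline and another at the end do not do that, and the final test reads any baseline difference between phone owners and non-owners as effect.

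**Working it through.** **Inputs from the protocol.** Two-sided 5% is assumed from "We will consider a 95% confidence interval", since sidedness is not stated. Power is 80% and n is 28 per group, or 34 with the allowance for loss (Study Population and Sample).

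**The plan's own figure.** For 80% versus 40%, the uncorrected size is [1.96√(2×0.6×0.4) + 0.84√(0.16+0.24)]² / 0.4² = 22.3, so 23. With continuity correction, (22.3/4)×[1+√(1+4/(22.3×0.4))]² = 27.1, so 28. Then 28×1.20 = 33.6, so 34. The stated sizes reproduce. They rest on two proportions, so they only supply n here.

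**Assumed inputs.** The protocol gives no pre-post correlation ρ, SD or mean change. I take normal data with equal SDs and vary ρ.

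**Literal reading: pre versus post as independent samples.** The unpaired test uses a standard error of σ√(2/n). The mean difference actually varies with σ√(2(1−ρ)/n). In units of the true standard error, the critical value rises from 1.96 to 1.96/√(1−ρ). With the shift set for 80% paired power (1.96+0.84 = 2.80), to a large-sample approximation:

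- type I error ≈ 2Φ(−1.96/√(1−ρ))
- power ≈ Φ(2.80 − 1.96/√(1−ρ))

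| ρ | 1.96/√(1−ρ) | Power, formula | Mann-Whitney power, simulated (n=28) | Type I error, simulated |
|---|---|---|---|---|
| 0.3 | 2.34 | 68% | about 65% | about 2% |
| 0.5 | 2.77 | 51% | about 48% | under 1% |
| 0.6 | 3.10 | 38% | about 38% | under 0.5% |
| 0.7 | 3.58 | 22% | about 24% | 0.1-0.2% |

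Simulated figures are good to a percentage point or two. On the same data Wilcoxon signed-rank has about 77% at every ρ. At ρ = 0 Mann-Whitney has 79%, so the loss comes from ignoring the pairing and not from using ranks. Results at n=34 are nearly the same.

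**Other reading: intervention versus control after treatment, no treatment effect.** Assume SD 15 mmHg, a baseline gap of 5 mmHg and ρ = 0.6. Two cases bracket the answer.

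- *Gap regresses* to 0.6×5 = 3 mmHg. At n=28 the standard error is 15√(2/28) = 4.01, so 3/4.01 = 0.75 and the rejection rate is about Φ(0.75−1.96)+Φ(−0.75−1.96) = 12% for a z test. Simulated Mann-Whitney gives about 11% (about 12% at n=34).
- *Gap persists* at 5 mmHg. Then 5/4.01 = 1.25 and the z-test rate is about 24%. Simulated Mann-Whitney gives about 22% at n=28 and 26% at n=34.

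**Which baseline-accounting analysis?** In the same two cases at n=28, a change-score test rejects about 8% of the time if the gap regresses and 5% if it persists. The baseline-adjusted post value (ANCOVA) gives about 5% and 9-10%. Neither is right in both cases.

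**The case against.** The strongest reply is that the sentence is only loosely worded. It follows directly on a between-group use of Mann-Whitney: "we will apply the Mann-Whitney test to compare the score between the groups before and after the intervention". The authors plainly know paired tests, because they name two of them just before. On that reading Mann-Whitney is a legitimate two-sample test. This stands as far as it goes: the between-group meaning is plausible, perhaps likelier. But it does not supply a test of the difference in change, and the sentence as printed says something else.

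The second reply is that the test is optional (*may*) while the paired t test is firm. This also stands. A reader might infer that a real fall in blood pressure is likely to be missed; that would need Mann-Whitney to replace the paired t test, which the protocol does not say.

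A reader might also infer that most of the power is thrown away. More than half is lost only from a correlation of about 0.6, and the protocol gives none. Nor does the literal reading create false positives; the test errs on the conservative side.

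Finally, the planned propensity score could be said to handle imbalance. It covers age, gender and socioeconomic status, not baseline blood pressure or MBG score, so it answers the point only in part. The choice of adjustment model can fairly be left to an analysis plan not shown here. An unpaired test worded for paired readings is a misstatement in this document.

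**Conclusion.** The point holds as a misworded and conflicting optional test on the primary outcome, not as a failure of the whole blood pressure analysis.

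On the literal wording, Mann-Whitney loses power at any positive within-patient correlation: from 80% to about 65% at 0.3 and about 24% at 0.7. This assumes normal data and equal SDs, with the correlations as assumptions.

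On the between-group reading, the test is valid for the samples, but two separate tests leave the difference in change untested, for blood pressure and for the MBG score. An assumed 5 mmHg imbalance would then raise the false-positive rate of the final test to between about 11% and 26%, depending on how far the gap regresses and on 28 or 34 per group. The 5 mmHg, the SD of 15 and the correlation of 0.6 are illustrative; the protocol gives no such figures.

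**What to change.** 1. Name Wilcoxon signed-rank as the nonparametric alternative to the paired t test for within-patient blood pressure, and say when it is used.
2. Limit Mann-Whitney to intervention versus control, and reword the sentence so that it names those two groups.
3. For the between-group comparison of blood pressure and MBG score, replace the separate before and after tests with one comparison that accounts for baseline: either change from baseline or the baseline-adjusted post value. Declare one as main and the other as a sensitivity analysis, because they differ when nonrandomised groups are unequal at baseline.

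The cost is about two sentences in the analysis section. No extra data collection or sample size is needed to make the change.
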